**Main research objective**

The main objective of this study is to test the *null hypothesis that the use of a chatbot such as Vitalk over a period of eight weeks does not result in different mental health outcomes in a treatment and control group* of health workers in Malawi. The null hypothesis will be tested in a two-arm RCT comparing the pre-treatment to post treatment scores using standardized scales for depression, anxiety, resilience, and burnout.

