All participants will be asked to take the standard mental health tests again in week four or five of the trial. This will be done virtually though email to all trial participants as a mid-trial check-in. After the end of the 56-day period, in week nine, both the treatment and control groups will be invited to attend a concluding half-day workshop, during which they shall again be evaluated on their general mental health using the previously completed mental health assessment tools. They shall then complete an anonymous online questionnaire on their experiences of interacting with the app or accessing the referred mental health links. Some participants will be invited to take part in focus group discussions (FGD) aimed at gaining detailed feedback about their experiences of using the two different interventions and the Vitalk app specifically (treatment group participants only for the latter). A mix of in-person and anonymous virtual FGDs are planned given the sensitive nature of mental health. A virtual FGD would be done without video and participants would only be identified by number not name. The use of two FGD formats, in-person and virtual, allows the comparison of how responses may differ between these two approaches. This study concludes with the workshop and FGDs in the 9^th^-week.

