**Sampling method**

Study participants will be recruited from all primary, secondary and tertiary care facilities within Blantyre district on a first come-first served basis. While this is a convenience sample based on self-selection, random assignment to treatment and control groups will counteract biases inherent to this approach. All participants are volunteers and agree to be assigned to either the treatment or the control group.

The required study population size for paired tests of correlated means was calculated using STATA 17 and is based on the following:

- Pre-post-treatment difference of 1.5 points on standard test scales
- Standard deviation of the difference = 6
- Power 80%
- Significance level 5%

This results in a minimum of 128 participants per study arm. Given the continuity experience – the proportion of participants completing the pre- and post-treatment assessments for depression, anxiety and stress – of 20-45% reported by Daley, Hungerbuehler et al. (2020), we assume that the dropout rate will be as high as 75% for at least one of the standard mental health assessments. This means that a sample of 512 participants will be required per study arm to yield an effective post intervention sample of 128. Furthermore, if 20% of potential study participants will not meet inclusion criteria or drop out for other reasons, about 640 people will need to be recruited initially per study arm. Therefore, the total number of participants for this study is 1280.

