**Data analysis method**

Data analysis will begin after the final workshop is concluded . There will be no interim sharing or analysis of trial data other than monitoring sample size in the two treatment arms and data completeness and appropriateness per data analysis plan for the entire trial data set. Data monitoring will be done by the trial manager.

The data analysis will start with descriptive statistics and bivariable analyses for mental health outcomes, resilience-building behaviors, intermediate outcomes, and user and study characteristics (non-modifiable and modifiable factors). This will include tests for central tendency and distribution.

The difference between treatment and control arms in mental health outcome scores at baseline, mid-study check-in and end-of-study-will be calculated using a linear, mixed-effect model for longitudinal data (e.g., STATA *mixed* or SPSS *MIXED*) applying maximum likelihood estimation, which takes into account any time trends. This method will allow the simultaneous modelling across different time points and estimate the difference in outcomes between the treatment and control groups across the entire study period.

This study will utilize Interpretative Phenomenological Analysis (IPA) as the main method of analysis for the qualitative data that shall be collected during the focus group discussions. Content Analysis will also be utilized to evaluate the participants’ experience in relation to pertinent social and psychological theories in order to explain attitudes and stigma behaviors. This process will also help to identify solutions and interventions that can be applied in order to ensure increased willingness to properly support health workers facing mental health challenges and a reduction in stigma against mental illness.

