Annex 1.2.3

**Data collected by the website for the control group and Vitalk for the treatment group**

1. Completed registrations (enrollment)
2. Completed GAD-7 and scores
3. Completed PHQ-9 and scores
4. Completed RS-14 and scores
5. Completed OLBI and scores
6. Frequency of use and results of Mood Meter
7. Completed resilience-building behavior assessment and results
   1. Frequency of Engaging in Cognitive Behavioral Stress Mgm’t over last 2 weeks
   2. Frequency of Practicing Mindfulness and Relaxation over last 2 weeks
   3. Frequency of Practicing Self-care over last 2 weeks
   4. Frequency of Connecting to Purpose over last 2 weeks
   5. Frequency of Connecting to Others over last 2 weeks
8. Program selected or clinical content accessed in Vitalk or pages accessed and links followed on control website
9. Frequency, timing and duration of interaction with control website or Vitalk
10. Number and frequency of questions asked
11. Number and frequency of no access to the internet
12. Number and frequency of technical support requested

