Annex 1.2.4

**Concluding Workshop Questionnaire: Treatment Group**

Thank you for joining us for the workshop today and for engaging with us as we have explored health workers’ psychosocial wellbeing and interacted with the Vitalk app over the past 56 days. We appreciate your time and participation!

We would like to ask you a few questions about your experience so that we can learn from this process and from your feedback. Your responses will be used to understand how the process went, what went well, and what improvements could be made in the future. All your responses will be anonymous and will not be linked to you now or in the future, and you can stop taking this survey at any time.

We are interested in your thoughts, so if you have anything to share that did not come up in the conversation today or that you want us to know, please feel free to share those thoughts on this form. If you have any questions or concerns, feel free to reach out to today's facilitator.

If you agree to this information and want to continue, please complete the following questions:

1. How many days have you actively used the Vitalk app after the first workshop?
   - 0 days
   - 1 to 7 days
   - 8 to 14 days
   - 15 to 21 days
   - 22 to 28 days
   - 29 to 35 days
   - 36 days or more
2. If you used the app less than 20 days, what was the reason for not using it more often?

(You can skip this question if you used the app 20 or more days)

1. How much do you agree with the following statement: "The Vitalk app helped me feel better"?
   - Completely disagree
   - Somewhat disagree
   - Neither agree nor disagree
   - Somewhat agree
   - Completely agree
2. What did you find the most enjoyable and/or most helpful when using the app?

1. What were the things that you did not like or found the least helpful when using the app?
2. What are the main benefits you got from using the Vitalk app?
3. How could we improve the app for the future?

1. How likely are you to recommend the Vitalk app to others?

| Not at all likely | | |  |  |  |  |  |  | Extremely likely | |
| --- | --- | --- | --- | --- | --- | --- | --- | --- | --- | --- |
| 0 O | 1 O | 2 O | 3 O | 4 O | 5 O | 6 O | 7 O | 8 O | 9 O | 10 O |

1. During these workshops on psychosocial wellbeing of health workers, I felt…

(check all that apply):

- - Energized
  - Renewed
  - Bored
  - Inspired
  - Overwhelmed
  - Angry
  - In agreement with the presenter
  - In disagreement with the presenter
  - Other

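### The stated 80% power belongs to a within-arm paired test and makes no allowance for assigned participants who give outcomes but make little or no use of Vitalk

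*Combined protocol and SAP*

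**What the plan says.** **Sizing.** The Sampling method section states: "The required study population size for paired tests of correlated means was calculated using STATA 17". Its inputs are "Pre-post-treatment difference of 1.5 points on standard test scales", an SD of the difference of 6, 80% power and a 5% significance level, giving 128 per arm. A dropout rate of up to 75% for at least one assessment raises this: "This means that a sample of 512 participants will be required per study arm to yield an effective post intervention sample of 128". A further 20% for ineligibility or other dropout gives 640 per arm and 1280 in total. The 75% is drawn from a 20-45% range in an earlier Vitalk study, which the section defines as completion of the assessments before and after treatment.

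**Who is tested.** The mid-trial tests go by email to all participants (Study period). For week nine, "both the treatment and control groups will be invited to attend a concluding half-day workshop", with no condition on use. Benefits/Impacts reimburses all participants for attending the workshops. The treatment-arm questionnaire (Annex 1.2.4) asks "How many days have you actively used the Vitalk app after the first workshop"; its answers start at zero days and 1 to 7 days, and a follow-up asks why use was below 20 days.

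**Analysis.** Under Data analysis method, a linear mixed model will "estimate the difference in outcomes between the treatment and control groups across the entire study period". No exclusion for low use is stated. The null hypothesis, framed for the two study arms, reads: "the use of a chatbot such as Vitalk over a period of eight weeks does not result in different mental health outcomes". Annex 1.2.3 has both platforms log "Frequency, timing and duration of interaction with control website or Vitalk".

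**The concern.** Missing outcomes and non-use of the app do different things to power. A participant with no week-nine score reduces the number analysed, and dividing by the completion rate is the right correction. A participant who is scored but did not use Vitalk stays in the analysis and pulls the mean treatment effect towards zero. Head-count inflation does not correct that: if the effect shrinks by a used fraction u, the number needed grows as 1/u squared. The plan corrects for the first and is silent on the second, although its own questionnaire anticipates it.

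Two things are at stake. Readers will take 80% as the chance of detecting a difference between arms, which is not what was calculated. And if the trial shows no difference, the comparison by assignment cannot by itself tell an ineffective chatbot from an unused one.

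**Working it through.** **1. Reproduce the plan's figures.** Inputs from Sampling method: difference 1.5, SD of the difference 6, significance 5%. Sidedness is not stated; two-sided is taken because it reproduces the result.
- Standardised difference: 1.5 / 6 = 0.25.
- Paired t-test, two-sided: n = 128, power 80.2%. A one-sided test would need 101, which does not match.
- 128 / 0.25 = 512; 512 / 0.80 = 640; 2 × 640 = 1280.

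All figures reproduce. The 80% is thus the power to detect a change from baseline within one arm.

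**2. Power for the between-arm comparison at the same n.** Assumptions: 1.5 is the difference between arms in mean change, SD of change is 6 in each arm, and 128 are analysed per arm.
- Standard error of the arm difference: 6 × √(2/128) = 0.75.
- Signal-to-error ratio: 1.5 / 0.75 = 2.0, against a two-sided critical value of about 1.96.
- Power: about 51% (51.3% by two-sample t, 51.6% by normal approximation).
- About 252 analysed per arm would be needed for 80%.

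No dilution has been applied yet.

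**3. Add dilution, conditionally.** Let u be the share of analysed treatment-arm participants who get the full effect. Suppose that 1.5 is the effect in users and that the rest gain nothing relative to control. The mean arm difference is 1.5 × u and the ratio is 2u. The documents give no value for u, so a range is shown.

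| Used fraction u | Arm difference | Ratio | Power, 128 per arm |
|---|---|---|---|
| 1.0 | 1.50 | 2.0 | about 51% |
| 0.9 | 1.35 | 1.8 | about 43% |
| 0.8 | 1.20 | 1.6 | about 36% |
| 0.5 | 0.75 | 1.0 | about 17% |

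The SD is held at 6. Allowing for the extra spread from mixing users and non-users was checked on the paired test and moved power by less than 1 point.

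**4. What would change these figures.** If 1.5 is already the average over everyone assigned, step 3 falls away and step 2 stands. Partial benefit in brief users would put the loss between the rows. The planned mixed model uses three time points and may differ somewhat from a two-sample test. More than 128 analysed per arm would raise power.

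**The case against.** The strongest objection is that the plan never calls 1.5 points the effect in users. It is listed only as a pre-post difference, and at 0.25 SD it is small beside the d of -0.81 or greater that the Background cites from the uncontrolled Vitalk study. It may be a cautious average that already allows for non-use. This stands: a reader might infer that the sizing gives every analysed participant the full effect and that 80% therefore fails through dilution, but the documents do not establish that. Nor do they establish the opposite. The cited study had no control group, standardisers may differ, and nothing says that 1.5 was discounted for non-use.

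A reader might also take the 20-45% as the fraction who will use Vitalk and compute very low power from it. The documents do not support that either. The figure is defined as assessment completion, and dividing by a completion rate is the correct treatment of it.

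Scaling the within-arm change by u would be wrong too. Non-users also get the workshop, weekly emails, mood meter and web resources, so their pre-post change need not be zero. This is why the dilution above is applied only to the difference between arms.

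Finally, the plan does not ignore use. Specific objectives 1 and 2 measure adoption and continuity, and test frequency and duration of use as predictors of outcome. Measured adoption would help to interpret a null result. But users select themselves, so the association in objective 2 is not protected by randomisation.

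**Conclusion.** The point holds in a limited form. It is established that the 80% refers to a within-arm paired test, that the only allowances are for lost data and ineligibility, and that non-users and brief users can be tested and are included in the comparison as assigned. For that comparison, power at 128 per arm is about 51% rather than 80%, if 1.5 is the arm difference in change and the SD is 6 per arm.

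The further loss from non-use is not established. It depends on two things that the documents leave open: what 1.5 represents, and how many week-nine attenders will have used the app. Should 1.5 be the effect in users, even 10% non-users would cost about 8 points (51% to 43%). This should be corrected because the stated power will be relied on, and correcting it is cheap.

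**What to change.** **Sampling method.** State whether 1.5 points is the effect in users or the average over everyone assigned. Keep loss of outcome data and non-use of Vitalk apart. Replace the single 80% with power for the between-arm, as-assigned comparison, with its assumptions. If 1.5 is the effect in users, show power over a range of used fractions, as in the table. Do not use the 20-45% as that fraction.

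**Data analysis method.** Keep the as-assigned mixed model as the main analysis. Pre-specify one secondary complier-average causal effect analysis, with random assignment as the instrument, logged Vitalk use (Annex 1.2.3, items 8 and 9) as the exposure, and adjustment for baseline score. Fix the definition of exposure in advance, for example any logged interaction after the app link is sent.

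State the limits of that analysis:
- Its intervals will be wider.
- It assumes that assignment without use has no effect. This is open to question, because the treatment arm receives daily and later alternate-day messages.
- It assumes that controls have no access to Vitalk.
- It depends on the missing-data assumption, which matters with up to 75% dropout.

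Present it as an aid to interpretation; it does not restore power.

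**Cost.** One rewritten paragraph, one extra analysis on data already collected, and a less favourable power statement. No added participants, visits or data collection.

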**Data collection instruments**

This study will collect data on intermediate outcomes related to Vitalk use, resilience-related health behaviors and final outcomes of treatment effectiveness measure as mental health status through standardized tests. In addition, data on independent determinants that potentially influence Vitalk use, resilience-building behaviors and mental health outcomes will be collected. Resilience-building behaviors can be determinants of mental health outcomes and will be measured as the frequency of five specific behaviors. As shown in Figure 1, these independent determinants fall into two groups: non-modifiable factors related to participant characteristics and modifiable factors related to the Vitalk app and study characteristics. While self-monitoring, knowledge and skills for mental health and coping mechanisms could be among modifiable determinants, the burden of data collection will be too high and outweigh any benefits of obtaining this information, because it would impact response rate negatively.

This study shall utilize the following standardized tests of various mental health indicators, in order to measure the effectiveness of the various mental health platforms that the treatment and control groups shall use:

*Generalized Anxiety Disorder (GAD-7)*

The GAD-7 is a 7-item self-report scale used to assess anxiety symptoms over the past 2 weeks (e.g., how often have you been bothered by feeling afraid something awful might happen). Scores range from 0 (not at all) to 3 (nearly every day) with a total of 21. The total scores are divided into four categories: none (0–4), mild (5–9), moderate (10–14) and severe (15+) symptoms. GAD-7 has been utilized effectively in Malawi and LMICs with comparable demographics (Mughal et al., 2020).

*The Patient Health Questionnaire (PHQ-9)*

The PHQ-9 is a 9 item self-report scale that evaluates symptoms of depression over the past 2 weeks (e.g., how often have you been bothered by feeling down, depressed, or hopeless). Item response options use a Likert scale ranging from 0 (not at all) to 3 (nearly every day). Total scores are divided into five categories: none (0–4), mild (5–9), moderate (10–14), moderately severe (15–19) and severe (20+) symptoms. The PHQ-9 has been widely used and validated in Malawi (Udedi et al., 2019).

*14-item Resilience Scale (RS–14)*

Resilience refers to the ability to withstand or adaptively recover from stressors. Resilience also promotes psychological and physical well-being. Resilience is negatively correlated with symptoms of generalized anxiety and posttraumatic stress and positively correlated with gratitude, optimism, and positive affect. The five characteristics of resilience are meaning and purposeful life, perseverance, equanimity, self-reliance, and existential aloneness (Wagnild, 2009a). Total scores are categorized as very low (14–56), low (57–64), on the low end (65–73), moderate (74–81), moderately high (82–90), and high (91–98). RS-14 has been validated and used in low and middle-income countries (Wagnild, 2009b; Siriwardhana, 2015)

*Oldenburg Burnout Inventory (OLBI)*

Burnout is linked to relatively high work requirements and limited resource availability for managing them, which leads to negative emotional states. Therefore, the discrepancy between resources and challenges creates a significant negative emotional state. The OLBI has 16 items, eight to describe exhaustion and eight to describe disengagement (Demerouti & Bakker, 2008). The questionnaire includes both straight and reversely worded items in both dimensions. Low, medium or high OLBI-D scores are based on scores above or below 1 standard deviation of the mean (mean= 2.15, SD = 0.52; ≤1.62= low, 1.63 to 2.67= medium, ≥2.68= high). OLBI has been validated and used in low and middle-income countries (Kaggwa et al., 2021).

Stress is not included in these assessments, because past evaluations have shown almost universally high stress levels pre- and post-intervention, which makes it impossible to use it as an outcome if there are no discriminating factors.

**Data management method**

The study will collect quantitative and qualitative data. All quantitative data will be collected online through the study portal and the Vitalk app. This will avoid any interviewer or researcher bias. Names, email addresses and phone numbers will be stored only during the trial phase. The data will be de-identified or anonymized prior to analysis and any data sharing by deleting all fields containing identifying information per the Safe Harbor Rule of the U.S. Health Insurance Portability and Accountability Act of 1996 (HIPAA) and subsequent guidance published by the Office for Civil Rights (OCR) at the U.S. Department of Health and Human Services (HHS) (HHS, 2008; HHS, 2012). A participant's clinical trial number will be the unique identifier retained, but it will be encrypted with a secret key to create a pseudonym. Only the trial manager will have a copy of the key. All other identifying information will be permanently deleted. All trial data will be securely stored in the cloud and access to de-identified data restricted to the research team. Access will be controlled by the trial manager for each individual researcher.

Qualitative data will be collected partly online and through focus group discussion (FGD). The concluding workshops in week seven after the end of the 56-day pilot period shall utilize an online questionnaire to be completed anonymously and a FGD guide to gain participant feedback on their experiences of using the app. All focus group discussions shall be recorded, along with notes collected during the FGDs. Once collected and transcribed, all data will be kept in locked cabinets at the investigator’s office. The recordings will be deleted after the completion of data analysis and the journal publication of the study is accepted.

**Data analysis method**

Data analysis will begin after the final workshop is concluded . There will be no interim sharing or analysis of trial data other than monitoring sample size in the two treatment arms and data completeness and appropriateness per data analysis plan for the entire trial data set. Data monitoring will be done by the trial manager.

The data analysis will start with descriptive statistics and bivariable analyses for mental health outcomes, resilience-building behaviors, intermediate outcomes, and user and study characteristics (non-modifiable and modifiable factors). This will include tests for central tendency and distribution.

The difference between treatment and control arms in mental health outcome scores at baseline, mid-study check-in and end-of-study-will be calculated using a linear, mixed-effect model for longitudinal data (e.g., STATA *mixed* or SPSS *MIXED*) applying maximum likelihood estimation, which takes into account any time trends. This method will allow the simultaneous modelling across different time points and estimate the difference in outcomes between the treatment and control groups across the entire study period.

This study will utilize Interpretative Phenomenological Analysis (IPA) as the main method of analysis for the qualitative data that shall be collected during the focus group discussions. Content Analysis will also be utilized to evaluate the participants’ experience in relation to pertinent social and psychological theories in order to explain attitudes and stigma behaviors. This process will also help to identify solutions and interventions that can be applied in order to ensure increased willingness to properly support health workers facing mental health challenges and a reduction in stigma against mental illness.

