**Specific research objectives**

In addition to testing the null hypothesis, this study intends to achieve the following specific objectives:

1. To evaluate whether the levels of engagement and continuity of use of Vitalk are adequate to meet the need for mental health support (rate of adoption and continuity).

2. To explore whether the frequency and duration of interaction with Vitalk are significant predictors of mental health outcomes (stickiness/intensity of use).

3. To establish whether the use of Vitalk significantly reduces the number and duration of sub-clinical and clinical episodes of depression, anxiety, resilience, and burnout over the study period (effectiveness).

4. To discover which features of Vitalk are liked or disliked; what improvements are suggested by users; and whether user experience drive stickiness (user experience).

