**Specific research questions**

The specific research questions of this study are as follows:

1. Are the levels of engagement and continuity of use of Vitalk adequate to meet the need for mental health support (rate of adoption and continuity)?

2. Are the frequency and duration of interaction with Vitalk statistically significant predictors of mental health outcomes (stickiness/intensity of use)?

3. Does the use of Vitalk significantly reduce the number and duration of sub-clinical and clinical episodes of depression, anxiety, resilience, and burnout over the study period (effectiveness)?

4. Which features of Vitalk are liked or disliked; what improvements are suggested by users; and does user experience drive stickiness (user experience)?

1. **Research Methodology**

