**Study period**

[figure not shown]
*Figure 2. Study process and timeline*

This trial is scheduled to span 56 calendar days, from the week beginning on the 4^th^ of October 2021 until the 26^th^ of November 2021. The entire process and timeline are shown in Figure 2. Study participants in both the treatment and control groups will begin their participation in this project by attending a half-day workshop prior to the start of the trial before October 4, which shall serve a dual purpose. Firstly, during this workshop participants shall receive a presentation about general tenets of mental health, how mental health affects work performance, the impact of one’s mental health upon their work, and a description of the four specific areas of mental health that will be assessed: namely anxiety, depression, resilience, and burnout. Secondly, participants will be provided with an overview over the study of ‘*an online self-help for mental wellbeing*’ and the eligibility criteria, but NO specifics about interventions in the treatment or control groups will be mentioned. Only information pertaining to both groups will be discussed.

At the workshop, participants will have the option to join the trial or to leave. Those opting to join will be directed to the study web-portal, provide their consent, complete a pre-screening to establish eligibility, and register for the trial. All participants eligible at this stage shall then complete the initial mental health assessment to assess the initial scores for depression, anxiety, resilience, and burnout. Anybody scoring at the severe level for any of the four scales or showing signs of suicidal ideation will be excluded from the trial and be provided with contacts to mental health professionals in Malawi and Vitalk-affiliated psychologists. All participants passing these final eligibility criteria shall be admitted to the trial and familiarized with links to mental wellbeing resources on the internet and contacts with local psychologists and mental health counselors.

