To achieve some degree of participant blinding to the intervention NO information about Vitalk or specifics about interventions in the treatment and control groups will be shared with workshop participants. Participants who completed registration will NOT be informed of their admission into the trial during the workshop; this will happen through an email after the workshop that provides the links to either Vitalk for the treatment group or the website for the control group or informs those not eligible for the trial. The trial manager will monitor whether the desired sample size is achieved; if it is not, additional recruitment efforts and workshops may be necessary.

Participants in the treatment group will receive daily messages and counseling for the first four weeks of the trial to encourage engagement with Viki, the Vitalk virtual counselor. This will change to every other day during weeks five though eight. Participants in the treatment and control group will receive weekly emails throughout the trial to encourage use of web mental health resources. Both groups will be asked to use the mood meter at least once a week to monitor mood changes. Those self-identifying with extreme negative emotions will be offered to take a relevant standard test again and encouraged to seek professional help.

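### Exploratory question 2 (does Vitalk use predict outcomes?) has only an unadjusted analysis stated; a model adjusted for baseline score should be written in

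*Combined protocol and SAP*

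**What the plan says.** Objective 2 under Specific research objectives is "To explore whether the frequency and duration of interaction with Vitalk are significant predictors of mental health outcomes". The matching research question uses statistical significance as its criterion: "Are the frequency and duration of interaction with Vitalk statistically significant predictors of mental health outcomes".

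Data analysis method describes the quantitative analysis in two steps. The first is "The data analysis will start with descriptive statistics and bivariable analyses for mental health outcomes, resilience-building behaviors, intermediate outcomes, and user and study characteristics". The second is a linear mixed-effects model over baseline, mid-study and end of study, whose purpose is to "estimate the difference in outcomes between the treatment and control groups across the entire study period". This serves the main objective, which rests on "comparing the pre-treatment to post treatment scores using standardized scales for depression, anxiety, resilience, and burnout".

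Data collection instruments treats Vitalk use as an intermediate outcome. It also says that data will be collected on determinants which may influence both Vitalk use and mental health outcomes. Annex 1.2.2 lists the participant characteristics (age, gender, therapy history, smartphone habits and others). Annex 1.2.3 logs the frequency, timing and duration of interaction, together with the scale scores.

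**The concern.** How much a participant uses the app is chosen, not randomised. If people with worse (or better) baseline scores use it more, use and follow-up score will be correlated even when use does nothing, because baseline score predicts follow-up score. The mixed model does not deal with this. Baseline enters it as a time point, but the contrast is between arms and there is no use term. That leaves the bivariable step as the only stated analysis that can answer question 2.

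The plan also does not say whether use would be related to the end score or to the change from baseline. Under confounding by baseline severity those two choices err in opposite directions, so the same data could suggest that use goes with worse outcomes or with better ones. At stake is the reading of one exploratory objective. The comparison of randomised arms does not depend on it.

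**Working it through.** **1. The plan's own figure.** Sampling method gives a difference of 1.5, SD of the difference 6, power 80% and significance level 5% (sidedness not stated; two-sided reproduces the result).
- Normal approximation: (1.960 + 0.842)² × (6/1.5)² = 125.6, so 126.
- Paired t-test: n = 128, power 0.8015, which matches the stated 128.
- Inflation: 128/(1 − 0.75) = 512; 512/(1 − 0.20) = 640; 2 × 640 = 1280. These match too.

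The check below takes 128 as the number of treatment-arm completers.

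**2. Assumptions not in the documents.** The correlation g between Vitalk use and baseline score is 0.1 to 0.3. The correlation ρ between baseline and follow-up score is 0.5 (range 0.3 to 0.7). Use has no effect of its own. Scores are standardised to the same SD at both times, so nothing depends on the units of a scale. The test is two-sided at 5%.

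**3. Spurious correlation.**
- Use with end score: r = ρg.
- Use with change score: r = (ρg − g)/√(2(1 − ρ)) = −g√((1 − ρ)/2).
- Use with end score given baseline: the partial covariance is ρg − ρg = 0.

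For any ρ between 0 and 1 and any non-zero g, the first two have opposite signs.

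**4. Chance of a significant result.** By the Fisher z approximation with n = 128, the standardised value is atanh(r) × √125, compared with 1.96. With ρ = 0.5:

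| g | r, end score | r, change score | Falsely significant (either score) | Baseline-adjusted |
|---|---|---|---|---|
| 0.1 | +0.05 | −0.05 | 8.7% | 5% |
| 0.2 | +0.10 | −0.10 | 20.2% | 5% |
| 0.3 | +0.15 | −0.15 | 39.4% | 5% |

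Simulation with 10,000 trials per cell agrees: 8.8%, 19.9% and 39.6% for end scores; 9.0%, 20.4% and 39.4% for change scores; 4.7% to 5.1% with baseline adjustment. A negative g gives the same rates with the signs reversed.

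**5. Sensitivity (simulated, g from 0.1 to 0.3).**
- ρ = 0.3: end score 6.4% to 16.8%, change score 9.9% to 52.5%.
- ρ = 0.7: end score 12.1% to 67.6%, change score 7.7% to 25.5%.
- At ρ = 0.5, with the 20% and 45% ends of the completion range cited in Sampling method: 0.20 × 512 = 102 completers gives 8% to 33%, and 0.45 × 512 = 230 gives 11% to 63%.
- With g = 0 the rate is 5% throughout.

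**The case against.** The strongest reply is that this is an omission and not a chosen method. The section says that analysis will start with bivariable work, does not assign that step to Objective 2, and mentions a data analysis plan that may be a separate document. Data collection instruments shows that the authors foresaw factors bearing on both use and outcome. Objective 2 is worded as exploration and speaks of predictors, so no dose effect is claimed. Most of this stands. A reader might infer that the plan commits to an unadjusted final answer; it does not, and the rates above show what could happen, not what is likely. What remains is that no later step for question 2 is written, while the question is to be settled by statistical significance.

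A reader might also want a new item on treatment-arm use of web resources. Admitted participants are "admitted to the trial and familiarized with links to mental wellbeing resources on the internet", and "Participants in the treatment and control group will receive weekly emails throughout the trial to encourage use of web mental health resources". The usage log covers "Program selected or clinical content accessed in Vitalk or pages accessed and links followed on control website", so outside web use in the treatment arm is not recorded. The documents do not make this a defect that needs new data. They say nothing on how much the links would be used or whether that use shifts scores. Data collection instruments limits added measures because of burden, and web use may itself follow from Vitalk use. Two 2-week recalls would cover about half of the eight weeks, and the extra term can cost power. It belongs among the stated limitations.

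**Conclusion.** The point holds as a minor one, confined to exploratory Objective 2 and question 2. The only stated analysis able to link Vitalk use to outcomes is unadjusted, and a better one is available from data already collected under the study ID. On the assumed inputs in step 2, false significance would be about 9% to 40% per scale at ρ = 0.5 against a nominal 5%, and 6% to 68% over ρ from 0.3 to 0.7. The true correlations are unknown, so size and direction cannot be taken from the documents. The opposite signs for end and change scores need only a non-zero use-baseline correlation and ρ between 0 and 1.

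Two further inferences are not supported. The randomised comparison is not weakened, because it uses no use term. The bias should not be quoted in scale points either: the four instruments differ in range and direction (a higher RS-14 score is better), and the SD of 6 in Sampling method is that of a difference, not of a score.

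**What to change.** In Data analysis method, add a sentence assigning an analysis to question 2. Within the treatment arm, regress the follow-up score on frequency and duration of Vitalk use (or fit a mixed model over the mid-study and end-of-study scores), adjusted for the baseline score on the same scale. As available, also adjust for characteristics already in Annex 1.2.2, such as age, gender, therapy history, and email, internet and chat-app use. Use the follow-up score as the outcome, which settles the choice between end and change scores. Report the result as an association, and state that confounding by motivation and by use of other resources remains.

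The cost is a few lines of text before analysis begins. No new data, visits or participants are needed, and baseline adjustment usually adds precision: at ρ = 0.5 it removes 0.5² = 25% of the outcome variance.
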